### Data collection and storage

The quality of all data collected will be regularly monitored by the site PI. Monitoring would be in accordance with Singapore Guidelines for Good Clinical Practice (SGGCP). The following elements will be monitored: recruitment proceeding as expected; cohort characteristics match the exclusion/inclusion criteria; deviations from protocol; timeliness, accuracy and confidentiality of all information in study documents and the central database. All study staff will be trained in the execution of study procedures including data collection and entry and training will be recorded in the study site file. For the purpose of this study, the electronic case report forms (eCRF) will serve as the source documentation. The data collected during the study will be entered into a central database by the study RA. The system will allow for audit tracking. Essential documents will be retained for a minimum of six years after the completion or discontinuation of the study.

### Determination of sample size

Whist a cohort OPAT study showed 100% cure, and another Singapore study failed to show any mortality from KLA [3,8], studies from Taiwan estimate a mortality of approximately 10% [4,10]. Given the inherent selection bias in the OPAT study, we estimate that overall 95% of patients will meet the primary endpoint of clinical cure in the control arm. The non-inferiority margin has been set at an absolute difference of 12% in the primary efficacy endpoint. This figure is justified because of the significant gains from use of oral antibiotics in terms of convenience and cost. The required sample size for a non-inferiority test for two binomial populations, with one-sided type 1 error 0.025, power 0.8, and non-inferiority margin 0.12, is 64 (in each arm) by use of the one-sided *z*-test with continuity correction. Assuming an attrition rate of 15%, a total of 152 patients would need to be recruited over two years.

### Statistical analysis

Data from all sites will be pooled for analysis. Descriptive statistics summarizing clinical observations data (for example, demographics) will be presented according to treatment arm. Continuous variables will be summarized using mean and standard deviation. Categorical variables will be summarized using the number of observations and percentages. All statistical analyses will be performed using SAS Version 9.3 or higher (SAS Institute Inc. [name]; [contact]; [contact]). Statistical analysis and programming support will be provided by the Singapore Clinical Research Institute (SCRI).

An intention-to-treat (ITT) population set is defined as all randomized patients. The treatment group of patients in the ITT set is the planned treatment group, that is, according to the randomization list planned prior to the study commencement. A per protocol population is defined as all randomized patients who have taken at least one dose of study treatment and has the primary endpoint measured. The treatment group of patients in the per-protocol population is according to the treatment actually received. Patients will be assigned to the group as per the first dose received of the study treatment. If patients are issued the incorrect study treatment, they should continue on this treatment and not switch. For example if a patient was randomized to oral antibiotics but the first treatment they received after randomization was IV antibiotics they should continue on IV antibiotics. Statistical analysis for safety data and compliance will be carried out on an as-treated basis. This is the same as the per protocol population but without the requirement that the primary endpoint is measured. An as-treated set is defined as all randomized patients who have taken at least one dose of study treatment. The treatment group of patients in the as-treated set is according to the treatment actually received.

Demographic characteristics (age, gender and so on) and other baseline characteristics (for example, clinical measures taken at baseline) will be summarized by appropriated descriptive statistics according to randomization arm, that is, frequency and percent for categorical variables; mean, median, standard deviation and minimum/maximum for continuous variables.

The primary analysis will be conducted on both the per-protocol population and intention to treat population. The study will claim non-inferiority based on the results of the analysis on both the per protocol and ITT population. For the ITT, drop outs will be imputed as clinical cure if they meet all of the following criteria: last two CRPs show a downward trend or are < 20; last two recorded temperature measurements < 38°C; contact established via phone call at day 84 (+/- 7 days) and patient reports they are symptom free. If the criteria are not met then the case will be imputed as a clinical failure. The exact method will be used to test the hypothesis of non-inferiority for the pre-specified non-inferiority margin of 12%. A two-sided 95% confidence interval (CI) for the treatment difference will be calculated and compared with the equivalence margin (12%). If this 95% CI for the treatment difference excludes the non-inferiority margin (12%) then there is evidence of non-inferiority.

The Fisher’s exact test will be used to compare 12 week mortality between the two treatment arms and the associated exact 95% confidence interval will be calculated using the Clopper and Pearson method. Additionally we will calculate the time from baseline to death for each treatment group using the Kaplan-Meier product-limit method, censoring at the 12 week assessment, those that withdraw or are lost to follow-up during the study period will be censored at the point of last follow-up. Fisher’s exact test and the Clopper and Pearson CI will be calculated for all other binary endpoints between the two treatment arms. The Mann–Whitney *U-*test will be used to compare the duration of inpatient stay and the length of time the subject requires medical leave following discharge between the two treatment arms.

Quality of life data will be measured using the WHOQOL-BREF. The two overall items (overall perception of quality of life and overall perception of health) and the four domain scores (physical, psychological, social and environmental) will be examined. The Student’s *t*-test will be used to compare the change from baseline at both 4 weeks and 12 weeks for each of these scores between treatment arms, as well as the change between 4 weeks and 12 weeks. In further exploratory analysis we will fit a mixed model to examine the effect of time and treatment on each of the four domain scores.

Duration of treatment and treatment compliance will be summarized by arm. For each subject in the treated population, an assessment of overall percentage compliance will be calculated as the percentage of patients who received at least 80% of prescribed antibiotics, as per protocol dosage. Compliance will be considered unknown if it cannot be calculated because of missing data. The number of patients discontinuing randomized investigational product, as well as the reason for discontinuation, will be summarized and listed.

An economic analysis will be performed. Admission costs will be obtained by searching the hospital’s data systems. Information retrieved will include diagnoses, tests, procedures and so on, for the period that participants are inpatients. The price of the specific antibiotics dispensed to each participant will be obtained from the hospital pharmacy database system. Following discharge, direct and indirect costs of all study related medical or non-medical healthcare utilization will be tracked via patient diaries and recordkeeping, inclusive of travel costs, days of work lost and the value of caregiver time. No discounting of costs will be necessary given the time span. The direct and indirect costs associated with the alternative treatment arms used will be calculated per patient at 12 weeks. The costs will be summarized using mean and median values and presented according to treatment arm. The primary cost-effectiveness ratio to be calculated will be the total incremental cost per clinical cure at 12 weeks between the two groups. The Student’s *t*-test will be used to compare the incremental cost effectiveness ratio (ICER) as well as mean costs between the two treatment groups. The bootstrap technique will be used to obtain confidence intervals around the estimated ICER. We will generate an empirical sampling distribution for the ICER using trial data by generating 1,000 independent samples of 100 cost and effect pairs from both the groups’ data drawn with replacement and calculating the ICER each time. We will then report 95% bias-adjusted confidence intervals for the ICER. Anticipating that actual cost and resource-use data is likely to be missing, we will impute values for the missing cases if necessary. The analysis will be performed using costs computed from both analytical perspectives. We also anticipate potential uncertainty around some values and assumptions made for unit costs. In such instances, sensitivity analysis will be performed to further explore the robustness of our results to the baseline assumptions that are made.

The analysis of safety endpoints will be on the as treated population. Numbers and percentages needing to stop study drug due to toxicity will be summarized between the two treatment arms; as will the numbers and percentages of reported clinical symptoms of moderate/severe grade (by body systems). Numbers and percentages of patients with at least one adverse event up to 12 weeks post randomization or 30 days post last study treatment (whichever is last) will be tabulated by treatment group and details of the event will be summarized. The numbers and percentages of serious adverse events will be tabulated by treatment group and the details will be summarized. Numbers needing to escalate antibiotics due to worsening infection or secondary infection at any point between randomization and Week 12 will be compared between arms using the Fisher’s exact test and the Clopper and Pearson CI will be calculated.

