### Randomization

After informed consent is signed, randomization into intervention or active control arms will be performed with a 1:1 allocation ratio. Balanced treatment assignments will be achieved using permuted block randomization, stratified by:

1) Abscess drainage (yes/no);

2) *K. pneumoniae* resistant to first-line agents (ceftriaxone or ciprofloxacin) (yes/no);

3) Study site.

The block length is determined by the study statistician and will not be made known to the clinical investigators or site personnel. All randomization will go through SCRI. Randomization will be done via direct web randomization. Authorized study center personnel will randomize the patient via a password protected internet website. The randomization system will then determine the treatment arm and provide the subject number to be used for the patient. The site monitor/clinical research associate (CRA) will be informed immediately in the event that the web randomization is not successful. Back-up randomization opaque envelopes (and related procedures) will also be prepared and provided to the site in case of internet failure.

Study arm allocation will not be blinded.

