### Study endpoints

The primary endpoint is 'clinical cure’, determined at Week 12 post-randomization, and defined as CRP < 20 mg/l, plus absence of documented fever ≥ 38°C in the preceding week, plus most recent abdominal imaging showing that the maximal diameter of the abscess has reduced.

The main secondary endpoint is 'clinical response’, determined at Week 4 post-randomization, and defined as CRP < 20 mg/l, plus absence of documented fever ≥ 38°C in the preceding week, plus most recent abdominal imaging showing that the maximal diameter of the abscess has reduced. Other secondary endpoints (assessed at Week 12) are:

• all-cause mortality at any point between randomization and Week 12;

• unplanned readmission for any cause at any point between hospital discharge and Week 12;

• unplanned need for drainage after enrollment at any point between randomization and Week 12 (the screening visit will document any plans for elective drainage);

• metastatic complications occurring at any point between randomization and Week 12;

• new *K. pneumoniae* bacteremia occurring at any point between the first negative blood culture, and Week 12, with the same strain of *K. pneumoniae* as the original blood culture or abscess fluid culture determined by antibiotic susceptibility pattern);

• length of hospital stay (from the date of randomization to the end of inpatient stay, censored at Week 12);

• length of time the subject requires medical leave following hospital discharge (censored at Week 12);

• subject quality of life as defined by the WHOQOL-BREF assessed at Week 4 and Week 12 post-randomization;

• overall cost of each treatment strategy from the payer and total societal perspective for the course of the study until the final 12 Week follow-up;

• level of adherence during the entire study period, assessed at 12 weeks. Subject deemed to be compliant if 80% or more of prescribed antibiotics have been taken.

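### The per-protocol set is in effect an as-treated completers set, so requiring it alongside ITT adds little protection against dilution by switching and non-adherence

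*Protocol article*

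**What the plan says.** All places are in the protocol article.

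- **Entry to the per-protocol set** (Statistical analysis): "all randomized patients who have taken at least one dose of study treatment and has the primary endpoint measured". Nothing is required on adherence, completion, eligibility or protocol deviations.
- **Grouping** (Statistical analysis): by treatment received, fixed at the start: "Patients will be assigned to the group as per the first dose received of the study treatment". A patient issued the wrong treatment is told to stay on it.
- **Relation to the as-treated set** (Statistical analysis): the section itself explains that the as-treated set is this same population with the measured-endpoint condition removed.
- **Decision rule** (Statistical analysis): "The study will claim non-inferiority based on the results of the analysis on both the per protocol and ITT population".
- **Adherence** (Study endpoints): "Subject deemed to be compliant if 80% or more of prescribed antibiotics have been taken". Study visits and procedures provides for pill counts and infusion-bottle counts. Neither is used to define an analysis set.
- **Withdrawal from treatment** (Withdrawal criteria): patients taken off the study intervention are still followed for efficacy, so they can have a Week 12 result and enter the per-protocol set.
- **Primary endpoint** (Study endpoints): CRP, fever and imaging at Week 12. All-cause mortality is a separate secondary endpoint. No text says how a death counts in the per-protocol set.

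**The concern.** A non-inferiority trial asks for a per-protocol analysis beside ITT because switching and poor adherence pull the arms together, and in this design that favours the claim. The per-protocol set is useful only if it removes such patients. Here an oral patient who takes one dose, moves to four weeks of IV treatment and attends at Week 12 is a per-protocol oral patient. So is one who takes a small part of the tablets. Both also count as oral in ITT.

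Switching is foreseeable. The trial is open-label, investigators may withdraw a patient from the intervention for safety or for a better option, and escalation of antibiotics is itself a listed safety endpoint.

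Grouping by first dose adds a second problem: a set that carries half of the confirmatory claim no longer compares the arms as randomised.

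**Working it through.** **1. The plan's own figure.** Inputs from Determination of sample size: "95% of patients will meet the primary endpoint of clinical cure in the control arm", one-sided alpha 0.025, power 0.80, margin 0.12, z-test with continuity correction. The oral cure rate is not stated; I take it as 95% too. Exact binomial enumeration with unpooled variance and correction ½(1/n₁ + 1/n₂) gives 64 per arm as the smallest n reaching 0.80 (power 0.807). With 15% attrition, 64 / 0.85 = 75.3, so 76 per arm and 152 in total. Both figures reproduce, and the sample size is not in dispute.

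**2. Who is in which set.** This follows from the definitions.

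| Patient, with a Week 12 result unless noted | ITT | Per-protocol as written |
|---|---|---|
| Randomised oral, one dose, then IV | oral | oral |
| Randomised oral, takes 20% of tablets | oral | oral |
| Randomised oral, first study dose IV, stays on IV | oral | IV |
| Dies before Week 12 | failure, if handled as a drop-out | outside the set on a plain reading |

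The first two rows are the dilution problem, and neither set deals with them.

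**3. Size of the dilution, on assumed inputs.** Let true cure be 95% IV and 83% oral, exactly at the margin. Let a share c of oral patients switch to IV after the first dose and gain a fraction b of the 12-point benefit. The oral group's cure rate is then 0.83 + 0.12 × c × b. The probability of claiming non-inferiority at 64 per arm is enumerated with the score test; the protocol says only that an exact method is used, so the score statistic is my choice.

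| c | b | Oral cure rate | False claim rate |
|---|---|---|---|
| 0 | – | 0.830 | 2.2% |
| 10% | 1 | 0.842 | 3.5% |
| 20% | 1 | 0.854 | 5.6% |
| 10% | ½ | 0.836 | 2.8% |
| 20% | ½ | 0.842 | 3.5% |

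The corrected z-test from the sample-size section gives nearly the same (2.2%, 3.6% and 5.8% for c = 0, 10% and 20% with b = 1). If switchers are removed and switching is unrelated to prognosis, the rate returns to about 2%, below the nominal 2.5%.

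**4. Deaths, on assumed counts.** Take 76 per arm, two other failures per arm, and two IV and five oral deaths.

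- Deaths counted as failures: 69/76 − 72/76 = 90.8% − 94.7% = −3.9 points; Wald 95% lower limit −12.2, which fails.
- Deaths dropped: 69/71 − 72/74 = 97.2% − 97.3% = −0.1 points; lower limit −5.4, which passes.

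The two analyses can differ sharply, but in this example ITT blocks the claim.

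**5. Cost of a stricter set.** By the corrected z-test, power is 0.81 at 64 per arm, 0.76 at 61, 0.73 at 58 and 0.71 at 54 (about 5%, 10% and 15% exclusions). Keeping 64 per arm after those exclusions and 15% attrition needs 2 × ⌈64 / (0.85 × 0.95)⌉ = 160, and by the same formula 168 or 178.

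**The case against.** **ITT must also pass.** This stands as a limit. A reader might infer that the per-protocol definition leaves the non-inferiority claim with no protection. The documents do not support that: the weakness lies in the per-protocol analysis, and it carries through to the claim only for dilution that ITT shares.

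**Deaths.** A reader might infer that the plan hides deaths or that losing them could produce a false claim. Neither follows. An ITT drop-out is imputed as cured only if, among other conditions, the patient is reached by phone around day 84 and is symptom free; a death handled as a drop-out cannot meet this and becomes a failure. Mortality also has its own Fisher test, confidence interval and Kaplan-Meier analysis. That deaths leave the per-protocol set is itself an inference from the endpoint's components. What remains is a gap in the wording.

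**First-dose grouping.** A reader might infer that one stray IV dose mislabels a patient who then takes oral treatment throughout. The section says such a patient should continue on IV, so the rule aligns the group with the treatment meant to follow, and it does remove dilution from wrong-route starts. It still departs from randomisation and does nothing about later switching.

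**Assumed magnitudes.** This also stands. The protocol gives no switching rate, and patients switched because they are deteriorating may not gain the full IV cure rate. Hence the range over b.

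**The replacement set is selected too.** Correct. Adherence and route changes happen after randomisation, so a conventional per-protocol set is not a randomised comparison either. That is a reason to keep ITT co-required, not to keep the present definition.

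**Conclusion.** The concern holds in this form. By the protocol's own description, the per-protocol set is the as-treated set restricted to patients with a measured endpoint. Because later switchers and non-adherers remain in both required sets, the per-protocol requirement adds little protection against dilution toward no difference. The rule is stated outright and forms part of the decision rule, so it is not a detail deferred to an analysis plan.

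The size is moderate and rests on assumptions. With a true difference at the margin and 64 per arm, 10% to 20% switching moves the false claim rate from 2.2% to between 2.8% and 5.6%, depending on the switching share and on whether switchers gain half or all of the IV benefit. The treatment of deaths needs one clarifying sentence and cannot by itself yield the claim.

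**What to change.** Redefine the per-protocol set in the protocol and carry the definition into the analysis plan:

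1. Analyse eligible patients in their randomised arm.
2. Require at least 80% of the allocated regimen, or a failure event reached before that point. The adherence data are already collected, but the threshold must be applied to the allocated regimen, since a switched patient could be fully compliant with what was later prescribed.
3. Exclude major deviations, including a route change that the protocol does not provide for. The oral extension after Week 4 in the IV arm is provided for and is not a deviation.
4. Exclude patients who started on the wrong route; do not move them to the other arm.
5. Keep first-dose grouping for the safety and compliance tables.
6. State that death before Week 12 is a failure in both the per-protocol and ITT sets.

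The text change is small and needs no new data. The real cost is power in the per-protocol analysis: about 0.81 at 64 per arm, 0.76 at 61 and 0.73 at 58. The plan should state this loss, or raise the target above 152 (about 160 for 5% exclusions, 168 for 10%). The new set is still selected on behaviour after randomisation, so non-inferiority in ITT must remain a condition of the claim.

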## Methods/design

### Study participants

The target number of subjects to be recruited is 152 over two years, across three academic teaching hospitals in Singapore (National University Hospital, Tan Tock Seng Hospital, and Singapore General Hospital). There is no restriction on subject recruitment by race or by gender. Pregnant and lactating women will be excluded from the study. Subjects will be identified by a research assistant (RA) who will be notified daily by radiology of all CT and US scans suggestive of liver abscess and by microbiology of all blood and fluid cultures positive for *K. pneumoniae*. The RA will screen eligible patients against study inclusion and exclusion criteria, and contact a study investigator to obtain informed consent. If the patient consents, the infectious diseases (ID) team will either take over management or co-manage the patient (with the primary physician’s agreement) to ensure that all elements of the protocol are adhered to. If the patient does not consent, the ID team will continue to provide consultation services.

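### Secondary and safety binary endpoints get a between-arm Fisher test with a one-sample Clopper-Pearson interval, so no confidence interval for the treatment effect is planned for them

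*Protocol article*

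**What the plan says.** The Statistical analysis section treats the primary endpoint and the other binary endpoints differently.

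- **Primary endpoint.** "The exact method will be used to test the hypothesis of non-inferiority" at the 12% margin, and a two-sided 95% confidence interval for the treatment difference is compared with that margin.
- **12-week mortality.** Fisher's exact test compares the arms, and the exact 95% interval described as going with it is Clopper-Pearson.
- **Other binary endpoints.** Fisher's exact test again, and "the Clopper and Pearson CI will be calculated for all other binary endpoints between the two treatment arms". This takes in the main secondary endpoint (Week 4 clinical response) and, from the Study endpoints section, unplanned readmission, unplanned drainage, metastatic complications and new bacteremia.
- **Antibiotic escalation.** The safety paragraph repeats the same pairing.

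On stratification, the Randomization section states: "Balanced treatment assignments will be achieved using permuted block randomization, stratified by" drainage ("Abscess drainage (yes/no"), resistance ("resistant to first-line agents (ceftriaxone or ciprofloxacin) (yes/no") and study site. The Statistical analysis section states: "Data from all sites will be pooled for analysis". It names Fisher's test, the Mann-Whitney test, Student's t-test and a mixed model in time and treatment. None is described as using a stratification factor.

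**The concern.** Clopper-Pearson inverts the binomial test for a single proportion. It yields one interval per arm and none for a difference or a ratio, so it is not the interval that corresponds to a two-arm Fisher test. The Objectives section sets the secondary objectives as comparisons of rates between the arms, yet for these endpoints the plan delivers only a p-value and two separate intervals.

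This matters more than usual in a non-inferiority trial. A non-significant Fisher test is not evidence that oral treatment is no worse. The interval for the difference carries that information, and readers without one tend to judge by whether the two per-arm intervals overlap, which is an unreliable guide.

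The lesser issue is efficiency. After blocked randomization within strata, an unstratified standard error overstates the variance of the difference when the strata predict outcome.

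**Working it through.** **1. The plan's own figure.** Inputs from Determination of sample size: 95% cure (taken for both arms), margin 0.12, one-sided 0.025, power 0.8, z-test with continuity correction. Enumerating the binomial outcomes for that test with an unpooled standard error and a correction of 1/n gives power 0.807 at 64 per arm, and below 0.80 at each smaller size tried. Closed-form approximations give 68, so 64 reproduces on the enumerated reading. Attrition: 64/0.85 = 75.3, rounded up to 76 per arm, total 152, as stated. The point below does not change the sample size.

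**2. What per-arm intervals show, and what they hide.** Illustrative counts (an assumption): 1/76 v 8/76 events.

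- Clopper-Pearson: 0.03% to 7.1%, and 4.7% to 19.7%. These overlap.
- Difference: 1.32% − 10.53% = −9.21 points.
- Wilson limits: 0.23% to 7.08%, and 5.43% to 19.42%.
- Newcombe lower limit: −9.21 − √[(1.32 − 0.23)² + (19.42 − 10.53)²] = −9.21 − 8.96 = −18.2 points.
- Newcombe upper limit: −9.21 + √[(7.08 − 1.32)² + (10.53 − 5.43)²] = −9.21 + 7.69 = −1.5 points.
- Fisher's test: p = 0.034.

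The overlapping per-arm intervals suggest no difference, while the interval for the difference excludes zero.

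**3. Week 4 response.** The Preliminary studies section gives a 73% response at four weeks in the cohort. Assuming 73% in both arms and 76 per arm, the Wald half-width is 1.96 × √(2 × 0.73 × 0.27/76) = 0.141, or about 14 points.

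**4. Stratification.** Two drainage levels × two resistance levels × three sites ("across three academic teaching hospitals in Singapore") make 12 strata, so 152/12 ≈ 13 patients each. The ratio of within-stratum to marginal variance is Σw·p(1 − p) / [p̄(1 − p̄)]. The article gives no cure rates by stratum, so the rates and splits below are assumptions (drained v undrained).

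| Cure rates | Split | Calculation | Ratio |
|---|---|---|---|
| 98% v 88% | 70:30 | (0.7 × 0.0196 + 0.3 × 0.1056)/0.0475 | 0.956 |
| 98% v 85% | 75:25 | (0.75 × 0.0196 + 0.25 × 0.1275)/0.0497 | 0.936 |
| 97% v 90% | 70:30 | (0.7 × 0.0291 + 0.3 × 0.09)/0.0484 | 0.979 |

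The variance reduction is therefore about 2% to 6%. At 64 per arm and 95% cure, the Wald half-width is 1.96 × √(2 × 0.95 × 0.05/64) = 7.6 points. A ratio of 0.956 shortens it by 1 − √0.956 = 2.2%, or about 0.17 points.

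Simulated power at 64 per arm with a simple Wald interval, with half the patients in each drainage stratum:

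- 98%/92%: 86.6% unstratified v 87.1% stratified.
- 100%/90%: 86.9% unstratified v 88.8% stratified.

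The asymptotic one-sided error of the unstratified test in these two cases is 0.0239 and 0.0220, both below 0.025.

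**The case against.** **Clopper-Pearson is valid for each arm's proportion, and that is a natural reading of the text.** This stands as far as it goes. It makes the wording loose and the intervals usable as descriptions of each arm, but it still leaves no effect interval for any of these comparisons. The method is named explicitly, so this is not a detail left open for an analysis plan that is not shown.

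**Only secondary and safety endpoints are touched.** This stands. A reader might infer that every binary endpoint lacks a proper interval. The documents do not support that, because clinical cure at Week 12 has a planned interval for the difference.

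**The stratification point can be overread.** A reader might infer that every comparison is unstratified. The text does not go that far: the exact method for the primary test is not specified, nor are the mixed-model covariates, and pooling sites does not rule out adjusting for site. Adjustment may sit in the analysis plan.

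**Drainage may not predict cure.** The Background reports worse outcomes without drainage only for abscesses over 5 cm, and not below that size, while the stratum is drainage yes/no. This weakens the case for a large gain, and it is why the figures above are ranges under assumption.

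**A stratified primary analysis would be sparse.** With about 13 patients per stratum and about 3 failures per arm expected among 64 (0.05 × 64 = 3.2), replacing an exact method with an approximate stratified one is debatable. This stands, and the stratified analysis is therefore proposed only as support.

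**Conclusion.** The interval point holds. As written, mortality, Week 4 response, the other secondary binary endpoints and antibiotic escalation have a between-arm test but no interval for the treatment effect. That conclusion follows from the text and needs no assumption; the ±14 points for Week 4 response rests on 73% in both arms and 76 patients per arm. The primary conclusion is unaffected.

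The stratification point holds in a limited form: no named comparison uses the randomization factors. Its size is small, a variance reduction of about 2% to 6% and roughly 0.5 to 2 points of power, all under stratum rates that the article does not give. Leaving the strata out is slightly conservative and does not invalidate the primary analysis. A reader might also infer that the loss falls on a trial already short of power. That is not supported, since 64 per arm and 152 in total reproduce under the stated test.

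**What to change.** - In the Statistical analysis section, for each secondary and safety binary comparison (mortality, Week 4 response, the other binary endpoints, antibiotic escalation), report the risk difference with a 95% interval by one named method: score (Miettinen-Nurminen), Newcombe or exact unconditional. Fisher's test can stay.
- State that Clopper-Pearson intervals describe single-arm rates only.
- Keep the planned exact analysis of the primary endpoint. Beside it, add a Mantel-Haenszel risk difference stratified by drainage and site, with sparse strata collapsed, as a supporting analysis.

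The cost is wording only. No further patients or data are needed, and the stratification factors are already recorded at randomization. The stratified interval is approximate with so few failures, which is why it should support the exact analysis and not replace it.
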